## Abstract

**Background:**

Metastatic prostate cancer remains a lethal malignancy that warrants novel supportive interventions for patients and their decision partners and proxies. Decision aids have been applied primarily to patients with localized disease, with minimal inclusion of patients with advanced prostate cancer and their decision partners. The use of a community patient navigator (CPN) has been shown to have a positive supportive role in health care, particularly with individuals from minority populations. Research is needed to evaluate decision support interventions tailored to the needs of advanced prostate cancer patients and their decision partners in diverse populations.

**Methods:**

Guided by Janis and Mann’s Conflict Model of Decision Making, the Cancer Health Aid to Manage Preferences and Improve Outcomes through Navigation (CHAMPION) is a randomized controlled trial to assess the feasibility and acceptability of a mobile health (mHealth), CPN-administered decision support intervention designed to facilitate communication between patients, their decision partners, and the healthcare team. Adult prostate cancer patients and their decision partners at three mid-Atlantic hospitals in the USA were randomized to receive enhanced usual care or the decision intervention. The CHAMPION intervention includes a theory-based decision-making process tutorial, immediate and health-related quality of life graphical summaries over time (using mHealth), values clarification via a balance sheet procedure with the CPN support during difficult decisions, and facilitated discussions with providers to enhance informed, shared decision-making.

**Discussion:**

The CHAMPION intervention is designed to leverage dynamic resources, such as CPN teams, mHealth technology, and theory-based information, to support decision-making for advanced prostate cancer patients and their decision partners. This intervention is intended to engage decision partners in addition to patients and represents a novel, sustainable, and scalable way to build on individual and community strengths. Patients from minority populations, in particular, may face unique challenges during clinical communication. CHAMPION emphasizes the inclusion of decision partners and CPNs as facilitators to help address these barriers to care. Thus, the CHAMPION intervention has the potential to positively impact patient and decision partner well-being by reducing decisional conflict and decision regret related to complex, treatment-based decisions, and to reduce cancer health disparities.

Trial registration

ClinicalTrials.govNCT03327103. Registered on 31 October 2017—retrospectively registered. World Health Organization Trial Registration Data Set included in Supplementary Materials.

**Supplementary Information:**

The online version contains supplementary material available at 10.1186/s13063-021-05602-0.

## Background

Recent advances in cancer therapy have contributed to limited knowledge about effective treatment and supportive care interventions for patients with advanced cancer and their decision partners. While a decline in the overall incidence of prostate cancer has been noted in recent years, advanced prostate cancer rates are on the rise. Rates are projected to increase through 2025, primarily among men younger than 70 years of age [1–3]. The annual burden of metastatic prostate cancer in the USA is estimated to increase 42% by 2025 [3]. Recent advances in cancer therapy have led to increased survival for many prostate cancer patients [4]. However, this benefit expands the need for knowledge about effective supportive care interventions for patients with advanced cancer and their decision partners. Despite improvements in cancer therapy, advanced prostate cancer remains a life-limiting disease that warrants novel supportive care interventions, particularly for patients with high disease burden facing complex, treatment-based decisions during the cancer process.

Treatment decisions—notably deciding when to start, change, or stop treatment—can overwhelm patients and their decisions partners and proxies. Decision partners have been identified as an important source of support for patients at these crucial decision points [5, 6]. A decision partner is a person who has a relationship with the patient and maintains a willingness to participate in decision making or proxy decision-making, understands the patient’s condition and anticipated treatment decisions, and demonstrates self-efficacy, the emotional capacity required for participation, as well as a willingness to fulfill several supportive roles, such as patient advocate [7].

When a patient’s disease progresses to an advanced stage and the decision-making capacity wanes, decision partners often step into the role of proxy decision-maker for treatment-related decision-making for their loved ones [8]. Decision partners are ideal proxy decision-makers due to their proximity to the patient and knowledge of the patient’s values and preferences. The proxy decision-making process has been shown to be associated with negative outcomes for the decision partner, including stress, guilt, or depression [9, 10]. Decision partners may experience an immense amount of decision-making burden related to decision-making, particularly when patients have limited decision-making capacity for reasons such as brain metastases or cognitive deficits related to treatment. Studies [11–13] have noted the value of decision partners in helping to make decisions for terminally ill patients when they are most vulnerable [14].

Interventions to increase the engagement of decision partners and enhance shared decision-making in the prostate cancer treatment decision-making process have the potential to (1) reduce decisional conflict and decision regret [15–18] and (2) improve the health-related quality of life (HRQOL) outcomes for patients and their decision partners, particularly in the realm of psychosocial wellness. Decisional conflict is the inclination to accept or reject a course of action at the same time [15]; decision regret is an undesirable, cognitively influenced emotion that is experienced when one wishes that the current situation would have been better if one had made a different decision [18–20]. A decision aid is one type of evidence-based intervention that promotes informed and shared health-related decision-making [21]. Although there is a growing body of literature describing the utility of decision aids in prostate cancer [22–24], to our knowledge, decision aids have been applied primarily to patients with localized disease, with an emphasis on treatment knowledge or options, with minimal inclusion of patients with advanced prostate cancer and their decision partners. Many decision aids are patient-directed; however, this orientation may not be appropriate in advanced cancer states, especially for minority patients who are less likely to make decisions alone [21]. Individuals with advanced cancer from minority groups with advanced cancer, particularly African Americans, are often faced with ineffective communication between themselves and their oncologist. This can lead to a breakdown in the effectiveness of cancer treatments and result in significant distress for the patients and their decision partners [25–27]. Targeted decision support interventions are needed that incorporate commonly noted African American values, such as spirituality, family and trusted others [25–27].

The role of the community patient navigator (CPN) has proliferated due to its demonstrated effectiveness in community outreach, social support, informal counseling, and health education [28]. CPNs have been associated with improved care access and reduced healthcare costs, particularly among minorities [29–31]. Mobile health (mHealth) tools, such as electronic tablets and smartphones, have an important healthcare role, such as the capacity to enhance communication between the oncologist and the patient, particularly those who are underserved [32–34]. mHealth technology can function as a resource to support patients and decision partners, aid in decision making, and help bridge health communication between the patient, decision partner, and oncologist [32, 35, 36]. Despite the growing role of CPNs in cancer care [37, 38] and the utility of interactive mHealth technologies, decision aid use by CPNs to improve patient outcomes has been mostly unexplored. Subsequently, there is an urgent need to describe and evaluate CPN-administered mHealth decision support interventions that are tailored to advanced prostate cancer patients and their decision partners and that address the unique needs of racial and ethnic minority populations.

The Cancer Health Aid to Manage Preferences and Improve Outcomes through Navigation (CHAMPION) study intervention involves an interactive mHealth decision aid delivered by CPNs, and includes measures of health-related QoL throughout the course of the patient’s illness trajectory. The intervention has been pilot tested [39, 40] for advanced prostate cancer patients to enhance informed, shared decision making. In present study, the role of the CPN in the decision-making process will also be assessed. CHAMPION is designed to improve decision-making processes, match patients’ and decision partners’ preference to participate in treatment decisions, enhance patient-provider communication, and enrich psychosocial health-related quality of life (HRQOL-PSY) outcomes for patients and their decision partners. The primary aims of this study are to decrease decisional conflict/uncertainty, decrease decision regret, enhance HRQL-PSY, assess participation preferences in decision-making, and examine potential differences by race (African American versus White and Others) related to using the CHAMPION intervention. Because low decision-making involvement is thought to contribute to cancer-related health disparities, this novel intervention has the potential to positively impact the decision-making process for patients and their decision partners with the inclusion of the CPN, clarifying and supporting the treatment decision-making process.

## Decision-making theoretical framework

Janis and Mann’s Conflict Model of Decision Making underpins the CHAMPION intervention [15, 16, 40]. This theory of decision-making proposes steps to promote good decision-making for consequential decisions in which perceived losses exist, no matter the choice. Stress is recognized as negatively affecting decision-making because decision-making requires high-level cognitive processes. With emphasis on the preconditions of risk, hope, and time by oncology providers, more time for clarifying options, values, and preferences (via use of a decision balance sheet), and increased provider support (structured discussions with providers), patients and their decision partners are supported in the decision-making process and may be less likely to feel regret or dwell on decisions out of their control. This theoretical framework has been applied to the CHAMPION study (a) as a brief decision-making process tutorial taught and reviewed with participants using an easy-recall method and (b) to predict outcomes for the patient-decision partner dyads.

## Methods/design

### Study design, setting, and population

The CHAMPION study is an ongoing randomized control trial to assess the effectiveness of a decision intervention (DI) compared to enhanced usual care (EUC) alone. Participants enter the study at one of three single-event decisions: (1) starting, (2) changing, or (3) stopping anti-cancer treatment. For example, a patient being monitored after primary cancer treatment who is diagnosed with disease progression and offered new treatment options would be eligible for this study. Alternatively, a patient who does not respond to, or experiences side effects from, their first choice of treatment and is now considering changing to a new treatment would also be eligible. An example of stopping treatment is a patient who has been on Androgen Deprivation Therapy and is considering stopping treatment. The unit of randomization is the patient-decision partner dyad, with stratification based upon the patient’s race (African American, White, or Other), and by decision event (starting, changing, or stopping anti-cancer treatment). Dyads will be randomly assigned after baseline data collection using a computerized random number generator weighted to have a greater number of DI than EUC dyads. Dyads will be randomized by a study team member, who will have access to sealed envelopes in the event that the computer system is not operational.

A pre-test/post-test design (see Fig. 1) for the three single-event decisions (starting, changing, or stopping anti-cancer treatment) is employed to assess change in HRQL-PSY, decisional conflict, and decision regret. Qualitative methods (post-intervention interviews) are combined with quantitative measurement to enhance the understanding of the patient-decision partner dyads’ experiences using the mHealth decision aid, particularly, in regard to their race and decision event. Patients and decision partners are randomly assigned as a dyad to one of two study arms: EUC or DI. EUC participants receive CPN-administered standard-of-care cancer educational materials not specific to decision making. DI participants receive CPN-administered standard-of-care cancer educational materials plus a previously piloted multicomponent intervention that is designed to facilitate decision partner involvement in the decision-making and communication within the patient-decision partner dyad, as well as between the dyad and the oncologist. Figure 2 displays the CHAMPION study design flow chart.

**Fig. 1 Fig1:**
[figure not shown]
Trial design schematic for schedule of enrollment, interventions, and assessments

**Fig. 2 Fig2:**
[figure not shown]
CHAMPION study design flow chart

The study setting includes three National Cancer Institute designated academic medical centers in the mid-Atlantic region of the USA: the University of Virginia (UVa), Johns Hopkins University (JHU), and Virginia Commonwealth University (VCU). The UVa Cancer Center predominantly serves rural areas in South, Southwest, Central, and North-Central Virginia [41] with approximately 11% of the catchment area residents being African American and 4% Hispanic. The Sydney Kimmel Comprehensive Cancer Center at JHU draws patients from Baltimore City and the surrounding area, as well as those seeking clinical trials, with approximately 20% of the patients being African American and 3% Hispanic. The VCU Massey Cancer Center predominantly serves rural areas in Central-East and Central-West Virginia [42, 43], with approximately 27% of the catchment area residents being African American and 6% Hispanic.

Patient inclusion criteria include the following: a diagnosis of stage III/IV prostate cancer, life expectancy of ≥ 6 months, Karnofsky Performance Status [44] ≥ 60, age ≥ 18 years, and the ability to understand English. Exclusion criteria include the following: severe psychiatric problem, prior non-prostate malignancy in the past 3 years (except treated basal cell/squamous cell skin cancer or superficial bladder cancer), and cognitive impairment. A s*evere psychiatric problem* is defined as inpatient psychiatric treatment in the past 6 months, current treatment with antipsychotic medication, current hallucinations, and/or current serious thoughts of suicide. Cognitive impairment is defined as an adjusted error score of > 5 on the Short Portable Mental Status Questionnaire or other issues preventing participation. A decision partner is defined in the eligibility criteria as a person that the patient identifies as supporting the patient in the decision-making. Consistent with the literature definitions [7], the decision partner is most often a spouse, but can also be an adult family member, friend, or spiritual advisor. In the present study, participants were asked to identify a single decision partner. For illustrative purposes, a ‘typical’ patient-decision partner dyad in this study appears as described in Table 1.

**Table 1 Tab1:** A “typical” CHAMPION study dyad (composite case)

	Age	Race	Ethnicity	Insurance	Employment
Patient	67	African American	Non-Hispanic	Public and private	Employed
Decision partner	68	African American	Non-Hispanic	Public	Retired
**Sample case history:** Patient was diagnosed in 2009 with regionally metastatic prostate cancer, underwent surgery to remove the prostate and regional lymph nodes at that time. In 2017, the patient developed an elevated PSA and was diagnosed with bone metastases after imaging and began hormonal treatment. Six months later, the patient experiences bone pain and undergoes additional imaging that shows further metastases. He and his decision partner are approached by the research team to seek consent for participation in CHAMPION following a consultation visit to discuss treatment options with the oncologist. Informed consent is obtained from the patient and the decision partner. Baseline data are collected and the patient-decision partner dyad are enrolled and randomized to the DI arm. The CPN reviews the decision theory and the dyad is introduced to the balance sheet activity via the practice “telling others about cancer” decision. The dyad is sent home with the preloaded mp3 player. Ahead of their return visit, the CPN assesses the dyad’s concerns and conducts the single-event decision (starting, changing or stopping treatment). During the decision visit with the oncologist, there is structured time to discuss any concerns that arose during the balance sheet activity. Over the next 9 months, the CPN maintains regular contact and provides graphical summaries of the patient’s HRQL-PSY symptoms, as reported by both the patient and the decision partner.					

The target sample for this trial is 158 patient-decision partner dyads. Quota sampling will be applied to obtain a study sample of at least 40% African American. Although the intervention was not developed for primary use in the African American population, this target was chosen to facilitate the team’s ability to estimate the impact of the intervention in the African American population. Although prostate cancer has high incidence in African American men, minority participation can be low; thus, recruitment strategies are being applied that focus on African American participants.

### Recruitment

Recruitment began in 2017 at UVa and JHU, and in 2019 at VCU. Participants are screened at each site using a variety of methods, including research team attendance at weekly clinical case discussions, manual chart review, and referrals from the clinical team. In this event-driven design, oncology clinic providers identify relevant events, such as the patient’s need to address starting, changing, or stopping treatment, and then refer eligible patient-decision partner dyads during weekly clinical trials meetings by teleconferences held at all institutions. In addition, the research teams attend weekly case discussions and discuss patients who may meet the eligibility criteria. The research team subsequently reviews these patients’ medical charts to determine eligibility. If a patient is eligible, the research team addresses the opportunity to participate in the study at the patient’s next clinical visit or over the telephone.

After confirming eligibility, the oncologist or another care provider introduces the study to the patient and decision partner. Patients experiencing serologic, radiographic, or symptom progression are contacted by the research team. The majority of patients and/or dyads are approached directly before or after their clinical visit with the medical oncologist. The research team reviews the study and, if the patient and/or the patient-decision partner dyad is willing, engages in an informed consent process to obtain oral consent or a signature from the patient and the decision partner, as approved by the facilities’ institutional review board (IRB). No data is planned to be used for further studies, which would constitute obtaining additional consent from current participants.

A previous version of the protocol required a decision partner for participation, but this requirement was removed after the study began, based on expert advice and research team discussion regarding the additional value of including patients without decision partners in the study. In the decision to include patients without decisional partners, there is a potential limitation in the analyses to compare between those patients who have decisional partners with those without decisional partners. We will plan to examine differences between dyads and single participants, particularly related to decisional conflict, regret, and quality of life.

Once the participant(s) consents to participate, the study team administers the baseline measures and randomizes the patient-decision partner dyad to either the EUC or DI group. Patient and/or patient decision partner dyads are enrolled in the study for approximately nine months. IRB approval is sought and obtained from each of the participating sites.

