### Intervention

The CHAMPION intervention incorporates mHealth technology to emphasize informed, shared decision-making for patients, decision partners and healthcare providers through values clarification, involvement preference, and HRQOL feedback [34, 35]. This decision aid is a comprehensive, cognitive-behavioral skills program that utilizes seven key components suggested by the theoretical framework to assist patients and their decision partners with goal-setting, establishing desired decision control, and facilitating discussions between oncology providers. The seven key decision aid components (see Table 2) are applied during any of three single-event decisions during the advanced cancer trajectory: (1) starting, (2) changing, or (3) stopping anti-cancer treatment [40].

**Table 2 Tab2:** Description of seven key decision aid components [41]

1. **Anticipatory guidance** for managing treatment side effects, quality-of-life and available therapies delivered via pamphlets from National Cancer Institute, Cancer Care National Office, or institutionally distributed.	
2. **Social support** provided by the decision partner’s participation in the study and interactions with the CPN.	
3. **Patient’s preferences for treatment decision-making participation** is assessed and shared with health care providers.	
4. **Decision-making process tutorial** communicates the importance of decision-making and satisfaction via an easy-recall teaching method that addresses (a) the purpose of the decision aid, (b) possible outcomes, (c) preconditions, (d) theory utility, (e) styles of decision making, (f) the steps/process of decision making, and (g) evaluation criteria. This is presented in a 12-min, easy-to-follow audio file and a follow-along transcript.	
5. **Normalization/experiential** context using the *“*Cancer Survival Toolbox: An Audio Resource Program*”* In this National Cancer Institute golden star award program, patients with specific cancer concerns demonstrate practical treatment tools for daily life.	
6. **Values clarification throughout the treatment decisions** through the use of a balance sheet, a simple table identifying the pros and cons for self and others (family and friends), resulting in values clarification for the patient-decision partner dyad. The balance sheet will be used during interactions within patient-decision partner dyads and with the CPN and oncology providers.	

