### Statistical analysis and power calculation

The main goal of this mixed-methods research is to test whether the decision support intervention is performing as hypothesized and warrants further research; thus, one-sided testing will be employed. The analysis plan assumes accrual (*N* = 158 dyads) for the quantitative portion of the study and a 15% dropout rate and assumes that the research team will have complete data on 134 dyads, providing approximately 89% power to detect an effect size of 0.5 for change in the main outcome measures for the DI group compared to no change in the EUC group using case-wise deletion. These calculations are informed by pilot data. Considering not all participants will be a dyad, and a smaller number will be single participants, it is unlikely that this would affect the power of the study. This will be reported in future dissemination materials once the study is completed.

For quantitative measures, descriptive analyses will be conducted as appropriate. Change in primary outcomes before and after the intervention will be assessed with analysis of covariance models that include the stratification factors (race and decision event), time, intervention arm, and a time-by-intervention-arm interaction. Additional analyses will assess whether the magnitude of change in primary outcome variables is similar between each member of the dyad using regression models that account for the correlation between each dyad and within participants over time. *Intention-to-treat* is defined as the analysis of all eligible patient-decision partner dyads by treatment as randomized, regardless of compliance with the intervention. Depending on the extent to which the data contain missing data, imputation will be considered for both the dyads and individual participants. Two methods will be used: (1) primary results will be based on an intention-to-treat analysis so that all eligible patients who entered the study will be included in the analyses regardless of compliance and (2) analyses will also include analysis of evaluable cases with more than 80% compliance (operationalized as completed all visits, all parts of the intervention but the home module, and had no other protocol violations) [48]. Using intention-to-treat analysis takes into consideration the bias of dropouts, but using both analyses provide more confidence in the conclusions of the trial if both analyses produce similar effects [48].

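### The partner requirement was dropped mid-trial, but the primary model has no partner-status term, and a whole-sample comparison of singles with dyads would be partly confounded with enrolment period

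*Protocol article*

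**What the plan says.** All references are to the protocol article.

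- **Recruitment** reports the eligibility change: "A previous version of the protocol required a decision partner for participation, but this requirement was removed after the study began". It gives neither the date of the change nor the number of patients who joined without a partner. It concedes that "there is a potential limitation in the analyses to compare between those patients who have decisional partners with those without decisional partners", and then states the plan: "We will plan to examine differences between dyads and single participants, particularly related to decisional conflict, regret, and quality of life". No model, contrast or adjustment is given for this comparison.
- **Study design, setting, and population** still randomises dyads, "with stratification based upon the patient’s race (African American, White, or Other), and by decision event (starting, changing, or stopping anti-cancer treatment").
- **Statistical analysis and power calculation** specifies "analysis of covariance models that include the stratification factors (race and decision event), time, intervention arm, and a time-by-intervention-arm interaction". Partner status, site and enrolment period are not among the terms. The section mentions single participants only to say that power is unlikely to suffer.
- **Intervention, Table 2** describes the social-support component as "provided by the decision partner’s participation in the study and interactions with the CPN". The values-clarification component is also built around the dyad.
- **Recruitment** and **Trial status** give the timing: two sites opened in 2017 and the third in 2019; recruitment began on 2 June 2017; version 1.11 is dated 24 August 2018; recruitment was to end about 1 September 2021.

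**The concern.** The eligibility change created a new kind of participant, and the written primary model was not updated for it. A single patient in the intervention arm cannot receive the partner's share of the social support, so partner status bears on the treatment as well as, plausibly, on the outcomes. Table 3 defines decision regret as a value at 9 months with no baseline, so change from baseline cannot absorb a stable difference between singles and dyads on that outcome.

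The second issue is the comparison of singles with dyads. Everyone enrolled before the change is a dyad by rule. A comparison using all participants therefore sets later-enrolled singles against a mixture of earlier and later dyads, with a different mix of sites because one site opened in 2019. Any drift in outcomes over calendar time would then be read partly as an effect of having a partner. A plain comparison of the two groups also would not show whether the intervention effect differs between them, which is the question raised by the partner's role in the intervention.

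**Working it through.** **1. The plan's own figure.** 158 × 0.85 = 134.3, so 134 complete dyads reproduces. With 67 per arm, an effect of 0.5 SD and one-sided alpha of 0.05 (the level is not stated and is assumed), the standard error is √(2/67) = 0.173. Power is Φ(0.5/0.173 − 1.645) = 89.4%, against about 89% stated. It is 88.3% at 1.5:1 allocation and 86.1% at 2:1. The article says only that the intervention arm is larger.

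**2. Effect on the arm comparison.** Allocation is random and independent of partner status, so the expected imbalance is zero and the unadjusted arm effect is unbiased. What remains is chance imbalance. Assume 16, 24 or 32 singles among 158, allocated without stratification on partner status (hypergeometric). The chance that the proportion of singles differs by 10 percentage points or more between arms is:

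| Singles (assumed) | 79:79 | 95:63 |
|---|---|---|
| 16 | 6.2% | 2.8% |
| 24 | 11.9% | 6.9% |
| 32 | 16.5% | 10.7% |

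If partner status shifted the outcome by 0.5 SD (assumed), a 10-point imbalance would move the arm estimate by 0.10 × 0.5 = 0.05 SD, against a standard error of about 0.17 SD.

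**3. Period confounding if all participants are used.** Let *e* be the difference in mean outcome between the later and earlier periods. All singles are late, so

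bias = *e* × [1 − P(late | dyad)] = *e* × (share of dyads enrolled before the change).

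With the change at fraction *t* of accrual and a share *q* of singles afterwards, that share is *t* / [*t* + (1 − *t*)(1 − *q*)].

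- Upper limit for *t*, if the change was in force by version 1.11 and accrual was even: 2 June 2017 to 24 August 2018 is 448 days, and 2 June 2017 to 1 September 2021 is 1,552 days. 448/1,552 = 0.289.
- *q* = 0.10: 0.289 / (0.289 + 0.711 × 0.90) = 0.31.
- *q* = 0.30: 0.289 / (0.289 + 0.711 × 0.70) = 0.37.
- For an assumed period effect of 0.3 SD, the bias is at most 0.3 × 0.31 = 0.09 to 0.3 × 0.37 = 0.11 SD.
- If the change came later, the share over the same *q* is 0.53 to 0.59 at *t* = 0.5 and 0.72 to 0.77 at *t* = 0.7.

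**4. Does restriction remove it?** A simulation of 5,000 trials used 134 completers, the change at half of accrual, 30% singles afterwards, a period effect of 0.3 SD and no true partner effect. The all-participant comparison was off by 0.178 SD on average (the formula gives 0.588 × 0.3 = 0.176). Restricted to post-change enrolment it was off by −0.001 SD. The arm effect averaged 0.502 for a true 0.500 with period left unadjusted. Partner status had no effect of its own in this simulation, so unbiasedness with respect to partner status rests on the randomisation argument in step 2.

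**5. Precision.** For an arm-by-partner-status interaction of 0.5 SD, SE = √[(1/n_single + 1/n_dyad) / (f(1 − f))], where f is the intervention-arm share. With 10% singles (13.4 and 120.6 of 134) and f = 0.5, SE = √(0.0829/0.25) = 0.576, and power at two-sided 0.05 is Φ(0.5/0.576 − 1.96) = 14%. From 5% to 40% singles it runs from about 9% to 29%, before restriction reduces the sample. For the main contrast of singles with dyads at 0.5 SD, power is 24%, 41%, 64%, 76% and 81% with 5%, 10%, 20%, 30% and 40% singles.

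**The case against.** The article fixes no crude analysis. It says only that differences will be examined, it admits a limitation in the sentence before, and the model may stand in an analysis plan that is not shown. That is fair, and it is why the confounding is stated here as conditional on using the whole sample. The admitted limitation names neither period nor site, however, and the primary model is a different matter: its terms are written out, so the absence of partner status there is not merely missing detail.

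Three stronger readings are tempting, and the documents do not support them.

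- *The comparison cannot show anything about partner status.* The confounding is partial. Dyads still enrol after the change, so restriction or adjustment separates period from partner status. Partner status is still not randomised, and no adjustment makes the contrast causal.
- *The primary arm comparison is biased.* It is not. A chance imbalance of the size in step 2 is ordinary sampling error, already covered by the standard error. That partner status is strongly prognostic is also not shown by any figure in the documents.
- *Partner status should become a randomisation stratum.* Race by decision event already gives 3 × 3 = 9 cells. A further factor would make 18, with few singles to fill them, late in accrual, and it would do nothing about period confounding.

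It also stands that no stated aim or primary outcome depends on comparing singles with dyads, which limits how much a distorted result would matter.

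**Conclusion.** The point holds in a limited form. The written primary model was not updated after the eligibility change and lacks a baseline factor that is known before randomisation and alters what the intervention delivers. The consequence is unadjusted chance imbalance and possibly lost precision, without bias in the arm effect.

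A comparison of singles with dyads on all participants would carry a bias of at most about 0.31 to 0.37 of any period effect. This rests on the change having been in force by version 1.11, even accrual, and 10% to 30% singles afterwards. The first is an inference and the other two are assumptions, as is any value for the period effect. A later change would make the bias larger. Site may add to it: if the change preceded 2019, the third site never had a dyad-only phase, so the earlier dyads come only from the other two sites. Even when correctly restricted, the comparison will be imprecise and can only be exploratory.

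**What to change.** 1. Add partner status at randomisation (single or dyad) as a covariate in the patient-level primary models. It does not apply to models of partner outcomes, where it does not vary.
2. Restrict the comparison of singles with dyads, and any arm-by-partner-status estimate, to patients enrolled after the requirement was removed at their site, and adjust for site.
3. Label both as exploratory and report estimates with confidence intervals.
4. Report the date of the change at each site and the number of single participants in each arm.

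The cost is one model degree of freedom, a smaller sample for the exploratory comparison, and an amendment to the analysis text filed with the review boards. The variable should already be on record, since partners consent and give baseline data before randomisation.
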